# Surgical treatment versus observation in moderate intermittent exotropia (SOMIX): study protocol for a randomized controlled trial

**DOI:** 10.1186/s13063-023-07189-0

**Published:** 2023-03-01

**Keywords:** Intermittent exotropia, Surgery, Observation, Randomized controlled trial, Binocular single vision

## Abstract

**Background:**

Intermittent exotropia (IXT) is the most common type of strabismus in China, but the best treatment and optimal timing of intervention for IXT remain controversial, particularly for children with moderate IXT who manifest obvious exodeviation frequently but with only partial impairment of binocular single vision. The lack of randomized controlled trial (RCT) evidence means that the true effectiveness of the surgical treatment in curing moderate IXT is still unknown. The SOMIX (surgical treatment versus observation in moderate intermittent exotropia) study has been designed to determine the long-term effectiveness of surgery for the treatment and the natural history of IXT among patients aged 5 to 18 years old.

**Methods/design:**

A total of 280 patients between 5 and 18 years of age with moderate IXT will be enrolled at Zhongshan Ophthalmic Center, Sun Yat-sen University, Guangzhou, China. After initial clinical assessment, all participants will be randomized to receive surgical treatment or observation, and then be followed up for 5 years. The primary objective is to compare the cure rate of IXT between the surgical treatment and observation group. The secondary objectives are to identify the predictive factors affecting long-term outcomes in each group and to observe the natural course of IXT.

**Discussion:**

The SOMIX trial will provide important guidance regarding the moderate IXT and its managements and modify the treatment strategies of IXT.

**Trial registration:**

ClinicalTrials.gov: NCT 02736526. Registered April 13, 2016

## Introduction

### Background

Strabismus is a common ophthalmic condition in children with prevalence of 1–5% [1–7], and intermittent exotropia (IXT) in which the eyes intermittently drift outward is one of the most common types of strabismus in childhood [8]. IXT left untreated can result in decreased stereopsis and amblyopia [9] and could eventually lead to intelligence and psychosocial problems [10, 11].

In clinical practice, the strabismus surgery can be performed in order to realign the eyes in severe IXT without binocular single vision (BSV). However, in children with mild IXT who have relatively normal BSV and good control of ocular alignment, the clinicians and parents prefer an observation rather than surgical or conservative treatments [12–14]. The best treatment and optimal timing of intervention for IXT remain unclear [15, 16], particularly for children with moderate IXT who manifest obvious exodeviation frequently but with only partial impairment of BSV. Previous retrospective study showed long-term surgical outcomes in small angle IXT did not appear to be more satisfying than observation [12]. The lack of randomized controlled trial (RCT) evidence means that the true effectiveness of the surgical treatment in curing moderate IXT is still unknown, or even when surgery is the preferred option, there is little agreement on the optimal timing for the surgery in this condition [15, 17, 18]. So, here, in the present study, we conducted a randomized trial of children 5 to 18 years of age with moderate IXT to assess the effectiveness of surgical treatment compared with observation for improving the ocular alignment and stereoacuity over long-term period of 5 years.

### Objectives

The primary objective of the SOMIX trial (NCT 02,736,526) is to compare the long-term cure rate of IXT between the surgical treatment and observation group. The secondary objectives are to identify the predictive factors affecting long-term outcomes in each group and to observe the natural course of IXT.

## Methods

### Study design

SOMIX is an RCT study to compare the long-term effectiveness of surgical treatment with observation prospectively in patients with moderate IXT (Fig. 1). No patient or public participated in the design of the protocol.

**Fig. 1 Fig1:**
[figure not shown]
SOMIX trial design

### Study setting

The study setting is the Zhongshan Ophthalmic Center (ZOC), Sun Yat-sen University, Guangzhou, China, which has 11 strabismus specialists and performs about 1000 IXT surgeries per year.

### Participants

The participants are children aged between 5 and 18 years referred to the clinics of ZOC with suspected IXT and subsequently diagnosed as IXT. Prior to any trial-specific procedure, the written informed consent for participation should be obtained from the parents or guardians of the participants.

### Sample size

The sample size for this study was calculated based on a standard two-sided trial with a continuous outcome, and the calculations assume 5% type I error with 80% power. According to an average 30% dropout rate in long-term follow-up period, we anticipate that we will require 280 total participants.

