### Allocation

#### Sequence generation

A blocked allocation (permuted random blocks of variable length) system is being used to randomly allocate patients to the two groups in a 1:1 ratio to intervention (group A) and control (group B) groups.

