### Proposed outcome measures

Primary outcome

For children with IXT, and their parents, the most relevant outcome from intervention is the restoration of normal ocular alignment, with associated cosmetic and functional benefits. The primary outcome of this RCT study will therefore be the difference in the cure rate of IXT between the surgical treatment and observation group.

Cure of IXT will be defined as:Realignment of ocular position at last follow-up, with deviation less than 8 PD both at near and distanceImprovement of near and distance stereoacuity ≥ 2 octaves (≥ 0.6 log arcsec)b)Secondary outcomeImprovement of NCSAge-specific evaluation of quality of life (IXTQ)Change of refraction

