### Statistical methods

The participant will be included in the analysis, once be randomized, regardless of whether or not the assigned intervention is received, in order to follow the “intention-to-treat” design.

For primary outcome, a chi-squared test will be carried out to evaluate the difference in cure rate at the final assessment between groups. For secondary outcome, a chi-squared test will be used to compare rates of improved NCS outcome between groups; Student’s *t*-tests will be used to assess the validity by matching individual initial and final scores.

Statistical significance was set at *p* < 0.05. Data were analyzed with the SPSS statistical package [SPSS (Statistical Package for the Social Sciences) Inc., Chicago, IL, USA], version 19.

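### The sample size and its 80% power are stated for a continuous outcome, but the primary outcome is a binary cure rate tested by chi-squared, so the stated power is not tied to the primary test

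*Protocol article*

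**What the plan says.** The Sample size section names the type of outcome on which the calculation rests: "The sample size for this study was calculated based on a standard two-sided trial with a continuous outcome". It continues that "the calculations assume 5% type I error with 80% power", and then: "According to an average 30% dropout rate in long-term follow-up period, we anticipate that we will require 280 total participants". It names no endpoint, difference, standard deviation or rate. Under Sequence generation, the trial will "randomly allocate patients to the two groups in a 1:1 ratio".

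The primary outcome, under Proposed outcome measures, is "the difference in the cure rate of IXT between the surgical treatment and observation group". Cure is defined by thresholds: a residual deviation below 8 PD at near and distance, and a stereoacuity gain of at least 2 octaves. The Abstract and the Objectives section also make the cure rate the primary objective. For the primary analysis, Statistical methods states that "a chi-squared test will be carried out to evaluate the difference in cure rate at the final assessment between groups".

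**The concern.** A sample size for a continuous outcome is driven by a mean difference and a standard deviation. The power of a chi-squared test on cure depends on the cure rate in each arm. A power figure worked out for the first kind of comparison does not carry over to the second.

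No section names a continuous primary or co-primary endpoint to which the calculation could belong. Deviation and stereoacuity are measured on scales, but the primary outcome cuts both at thresholds. The quality-of-life score and change of refraction are listed only as secondary outcomes.

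What is at stake is how the result will be read. If the trial finds no significant difference, a reader may set that against the claimed 80% power and conclude that a worthwhile benefit of surgery has been ruled out. The article does not say what size of cure-rate difference the 80% refers to, and its stated basis cannot supply one.

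**Working it through.** **Inputs from the protocol article.** Two-sided test, alpha 0.05, power 0.80, dropout 30% and total 280 (Sample size); 1:1 allocation (Sequence generation). Hence 280 / 2 = 140 per arm randomised, and 280 × 0.70 = 196 evaluable, or 98 per arm.

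**Step 1: can 280 be reproduced on the stated basis?** For two means, n per arm = 2(1.960 + 0.842)² / d², where d is the standardised difference. No d is given, so 280 cannot be reproduced, only back-solved: d = 2.802 × √(2/98) = 0.40. Going forward from d = 0.40, n = 98.1 per arm and 2 × 98.1 / 0.70 = 280.3 in total. If 98.1 is first rounded up to 99, the total is 198 / 0.70 = 283.

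The match does not identify the method. A two-proportion calculation for 40% vs 60% needs 97 per arm, and 194 / 0.70 = 278 after rounding up. The finding therefore rests on the wording of the Sample size section, not on the number 280.

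**Step 2: power of the test that will be run.** Normal approximation with pooled variance under the null hypothesis, no continuity correction:

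power = Φ{ [ |p₁ − p₂|√n − 1.960 √(2p̄(1 − p̄)) ] / √(p₁(1 − p₁) + p₂(1 − p₂)) }, where p̄ = (p₁ + p₂)/2.

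Example, 40% vs 55% with n = 98: 0.15 × √98 = 1.485; 1.960 × √0.49875 = 1.384; √(0.24 + 0.2475) = 0.698; (1.485 − 1.384) / 0.698 = 0.144; Φ(0.144) = 0.56.

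All cure rates below are assumptions; the article states none. The last column is the formula solved for 80% power.

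| Assumed observation cure rate | Power, 15-point difference | Power, 20-point difference | Difference giving 80% power |
|---|---|---|---|
| 5% | 89% | 98% | 12.6 points |
| 10% | 79% | 94% | 15.1 points |
| 20% | 65% | 87% | 18.1 points |
| 30% | 58% | 82% | 19.5 points |
| 40% | 56% | 80% | 19.9 points |

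**Step 3: sensitivity to the handling of dropout.** The table treats the 30% lost as unevaluable. Statistical methods includes everyone randomised but gives no rule for missing outcomes. If, as a further assumption, all those lost counted as not cured with 140 per arm, 30% vs 50% would become 21% vs 35% with 74% power, and 10% vs 30% would become 7% vs 21% with 93% power. The answer again depends on rates that the article does not state.

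**The case against.** The strongest reply is that nothing is shown to be short. The word continuous may be a slip for a calculation done on proportions. Entry requires at least 15 PD at distance and abnormal stereopsis, while cure requires under 8 PD at near and distance plus a 2-octave gain, so cure without surgery could well be uncommon. At observation rates of 5% to 10%, 280 gives good power for a 20-point gain. The mismatch leaves the type I error, the primary test and the effect estimate untouched, and a null result should in any case be read from its confidence interval. Missing effect sizes may simply have been condensed out of a journal article.

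Much of this stands. The absence of an effect size carries no weight here. Low cure rates under observation are plausible, although the article states neither low nor high ones. A slip is possible, but nothing in the text supports it, and it would still need correcting.

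What does not yield is the contradiction. The article positively states one outcome type for the calculation and another for the primary outcome and its test, and a fuller document could not make both correct.

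A reader might also take the d = 0.40 back-solve as proof of what was calculated. It is not: 0.40 is not a stated input, and proportions reach almost the same total.

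**Conclusion.** Wrong as written. The 80% power is attached to a continuous outcome, while the trial will be decided by a chi-squared comparison of cure rates, and no section reconciles the two.

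A reader might infer that the trial is underpowered or that 280 is too few. The documents do not support that. Without stated cure rates no shortfall can be shown: over assumed observation rates of 5% to 40%, with 98 evaluable per arm, power for a 15-point difference ranges from 89% to 56%, and a 20-point difference reaches at least 80% throughout. What can be said is that the smallest difference detectable with 80% power moves from about 13 to about 20 points over that range, and the article does not tell the reader where in it the trial sits. These figures assume equal arms, exactly 30% loss in each, and the normal approximation without continuity correction.

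**What to change.** Keep the sample size at 280.

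- Withdraw the continuous-outcome statement, or correct it if it was a slip, and disclose the endpoint and inputs originally used.
- Add a two-proportion calculation for the chi-squared test. Trial status records recruitment from November 2015, extended up to October 2022, so a calculation that was not the original one should be labelled retrospective and not presented as a design assumption.
- State in it that about 98 evaluable children per arm give 80% power for absolute differences of at least about 13, 15, 18, 19.5 and 20 points at assumed observation cure rates of 5%, 10%, 20%, 30% and 40%.

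This costs rewording and one recalculated table, with no extra patients and no change to the design or the primary test. The downside is that the stated power becomes conditional and may look less favourable than a flat 80%.

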### Clinical tests

The following clinical assessments are undertaken at each visit:Binocular single vision (BSV) testing: simultaneous perception, motor fusion, and distance stereopsis using synoptophore; near and distance stereopsis using Titmus test and Randot testBest corrected visual acuity (BCVA)Measurement of ocular alignment using the prism and alternative cover test (PACT) at near and distanceOcular motility examinationMeasurement of control of alignment using revised Newcastle control score (NCS)Evaluation of quality of life using Intermittent exotropia questionnaire (IXTQ) [19, 20]Cycloplegic refractionRoutine ocular examination of anterior segment, fundus, and ocular motility

### Eligibility criteria

#### Inclusion criteria

Age between 5 and 18 yearsEvidence of IXT on the basis of clinical examination: one eye intermittently drifts outward with minimum alternative exodeviation of 15 prism diopters (PD) in the distance; normal ocular motilityNo previous treatment for IXT (including patching, surgery, over-minus lens, vision therapy, and botulinum toxin)Presence of simultaneous perception and motor fusion documented using synoptophore but abnormal near and distance stereopsis using Titmus test and Randot test (stereoacuity of > 60 arcsec in the Titmus test or > 63 arcsec in the Randot test is defined as “abnormal stereopsis”)BCVA: 0.7 or better at age of 5 to < 6; 0.8 or better at age ≥ 6No ongoing or planned amblyopia treatment

#### Exclusion criteria

Moderate to severe refractive errors: spherical equivalent refraction (SER) >  + 2.00 diopters (D) or <  − 3.00 D (the preexisting refractive errors should be corrected with spectacles)Anisometropia > 1.50 DStructural ocular pathologySignificant systemic disorders (for example, neurodevelopmental delay)Unable to visit on a regular follow-up (family planning to move out of area)

#### Dropout criteria

Patients in the intervention group with adverse event or serious adverse event following strabismus surgeryPatients in the control group with a constant strabismus appears to be developing or whose parents request strabismus surgery

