**Fig. 2 Fig2:**
[figure not shown]
Standard protocol item. The follow-up visits schedule and corresponding clinical assessments. D, day; W, week; M, month; Y, year; BSV, binocular single vision; BCVA, best corrected visual acuity; PACT, prism and alternative cover test; NCS, Newcastle control score; IXTQ, intermittent exotropia questionnaire

Children in the observation group will be offered surgical treatment if a constant strabismus appears to be developing or parents request surgery and the responsible clinical team agrees that this is appropriate.

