### Data management

#### Data collection

An electronic data capture (EDC) system will be used to collect study data, including baseline characteristics and follow-up clinical evaluations. Participants will be mandatorily followed up regularly in order to access the necessary information.

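### Dropout criteria based on adverse events (surgery) and deterioration or a request for surgery (controls) conflict with 5-year follow-up of all children and intention-to-treat analysis, if dropout ends assessment

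*Protocol article*

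**What the plan says.** The Dropout criteria, under Eligibility criteria in the protocol article, contain two rules. In the surgery arm: "Patients in the intervention group with adverse event or serious adverse event following strabismus" surgery. In the observation arm: patients "in the control group with a constant strabismus appears to be developing or whose parents request strabismus surgery". The first sets no threshold for severity or relatedness.

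Other sections describe follow-up and analysis:

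- Abstract, Methods/design: "all participants will be randomized to receive surgical treatment or observation, and then be followed up for 5 years".
- Data collection: "Participants will be mandatorily followed up regularly in order to access the necessary information".
- Statistical methods: every randomised child is analysed, whatever treatment was received, and cure rates are compared at the final assessment by a chi-squared test.
- Proposed outcome measures: the first element of cure is "Realignment of ocular position at last follow-up".
- Sample size: "According to an average 30% dropout rate in long-term follow-up period", the total is set at 280.
- Interventions, text after Fig. 2: controls are offered surgery "if a constant strabismus appears to be developing or parents request surgery and the responsible clinical team agrees that this is appropriate".
- Potential risks and adverse events: adverse events are recorded and treated, and deterioration is managed throughout follow-up.

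The article nowhere says whether a child who meets a dropout criterion is still assessed at later visits.

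**The concern.** The triggers differ by arm and may well be related to outcome: complications on one side, deterioration or dissatisfaction on the other. If meeting one ends assessment, the trial's own rule creates informative missing data in the primary outcome. Intention-to-treat fixes who is counted and in which arm. It cannot supply a 5-year result that was never measured.

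Two things could then happen to a dropped child. Deletion from the comparison overstates surgical cure whenever cure is less common after an adverse event than without one. Scoring at an early visit, which the last-follow-up wording would permit, can push surgical cure either way. The control arm's error under deletion can also take either sign.

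A secondary objective is affected too. The Objectives include the aim "to observe the natural course of IXT", and dropping unoperated controls when they deteriorate, or when a parent asks for surgery, cuts that course short.

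**Working it through.** **1. What dropout means here.** Two readings are possible.

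- *Assessment ends.* This matches the Sample size section, where dropout is loss over long-term follow-up. Taken at face value, the 30% allowance leaves 280 × 0.70 = 196 evaluable children, 98 per arm at 1:1. The 280 itself cannot be reproduced because no effect size is given, and the point does not depend on it.
- *Only assigned management ends.* This could fit a control who crosses over. It hardly fits the surgery rule, because the operation is complete when the adverse event occurs. Nor does it fit every control. The Dropout criteria act on a parental request alone, whereas the Interventions section also requires the clinical team's agreement before surgery is offered. A control whose request is declined is unoperated and still under observation, yet meets a dropout criterion.

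On the first reading, the Dropout criteria cannot stand with 5-year follow-up of all, mandatory follow-up, and a final-assessment comparison of all randomised children.

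**2. Illustration of size.** The article gives no event, crossover or cure rates, so every rate here is an assumption. Arm size is 280 / 2 = 140.

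*Surgery arm.* Let q be the proportion with an adverse event, c0 = 0.50 cure without one and c1 = 0.20 cure with one. At q = 0.10 (14 children), true cure is 0.90 × 0.50 + 0.10 × 0.20 = 0.47.

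- Deletion error = q(c0 − c1): +0.015 at q = 0.05, +0.03 at q = 0.10, +0.06 at q = 0.20.
- Early-visit scoring at q = 0.10: 0.10 × (0 − 0.20) = −0.02 if none is yet cured at that visit; 0.10 × (0.50 − 0.20) = +0.03 if half are.

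*Control arm.* Let r = 0.20 be the proportion dropped (28 children), d0 = 0.10 cure in those who stay, and d1 the final cure in those dropped, from 0 to 0.47 (the surgical rate above).

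- Deletion error = r(d0 − d1): 0.20 × 0.10 = +0.02 at d1 = 0; 0.20 × (0.10 − 0.47) = −0.074 at d1 = 0.47.
- Early-visit scoring as not cured: 0 at d1 = 0; 0.20 × (0 − 0.47) = −0.094 at d1 = 0.47. If cure after crossover surgery counts as not cured, the error is 0.

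*Difference, surgery minus control, deletion in both arms* (q = 0.10, r = 0.20):

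| Assumption | True difference | Observed | Error |
|---|---|---|---|
| d1 = 0 | 0.47 − 0.08 = 0.39 | 0.50 − 0.10 = 0.40 | +0.01 |
| d1 = 0.47 | 0.47 − 0.174 = 0.296 | 0.40 | +0.104 |
| c1 = c0 = 0.50, d1 = 0 | 0.50 − 0.08 = 0.42 | 0.40 | −0.02 |

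True control cure is 0.80 × 0.10 + 0.20 × d1, which gives 0.08 and 0.174.

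**3. A second set of assumptions.** Take true cure of 40% and 20%, with 10% of the surgery arm (none cured) and 30% of controls deleted. Observed surgical cure is 0.40 / 0.90 = 0.444. Observed control cure is 0.20 / 0.70 = 0.286 if no dropped control would be cured, or (0.20 − 0.30 × 0.40) / 0.70 = 0.114 if 40% would be. The true 20-point difference appears as 15.9 or 33.0 points. With equal true rates of 30% and the same deletions, the apparent difference is 0.333 − 0.429 = −9.5 points if no dropped control would be cured, or 0.333 − 0.300 = +3.3 points if 30% would be. There is no bias if dropped children have the same cure rate as the rest of their arm.

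**The case against.** The strongest reply is that the conflict is conditional. The article never says that assessment stops or that these children are deleted. Its intention-to-treat statement covers controls who cross over, follow-up is called mandatory, deterioration is managed throughout follow-up, and the offer of surgery sits within the follow-up text. For controls, leaving assigned management while staying in follow-up would reconcile most sections. Last follow-up may simply mean the 5-year visit. The full protocol is not shown, and handling of crossover and missing outcomes is commonly left to it or to the SAP.

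Part of this stands. The text does not prove that anyone is removed, and the control rule is easier to read benignly than the surgery rule. The numerical range rests wholly on assumed rates. Its +10.4 end needs dropped controls to be cured at the full surgical rate, with those cures credited to observation; if crossover counts as not cured, the base-case deletion error is only +1. The natural-course loss concerns only controls who meet a criterion and remain unoperated.

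The rest does not remove the problem. The benign reading hardly fits the surgery criterion, nor a control dropped on request alone. Handling of missing data may be left to the SAP, but a rule that generates missing data is trial conduct, and the article states that rule. The section on risks does not say that outcome assessment continues after these events.

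**Conclusion.** The concern holds as a conditional inconsistency: if dropout carries its ordinary meaning, the Dropout criteria contradict the follow-up and analysis commitments and remove children from the primary outcome on arm-specific, plausibly outcome-related events. The surgery-arm rule is the clearest fault, because it covers any adverse event and leaves no treatment to discontinue.

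Neither size nor direction can be determined from the article. The illustrative error of +1 to +10.4 points, or −2, shows only that the distortion can be large enough to matter and that its sign is not fixed. The plan should be corrected. Confidence is medium because dropout is undefined.

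**What to change.** Remove these events from the Dropout criteria, or redefine them as discontinuation of assigned management only. State that affected children keep the existing visit schedule to the 5-year assessment and are analysed in their randomised arm. Limit dropout to withdrawal of consent or loss of contact. How cure after crossover surgery is counted can be prespecified separately. Treatment of adverse events and the conditional offer of surgery to controls stay as they are.

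The cost is a short amendment plus visits already scheduled. Recruitment began in November 2015, so outcomes of children already dropped may be only partly recoverable. It was extended to October 2022, and the 5-year visit of a child enrolled then falls in October 2027, so later entrants can still be protected. The surgical result may look slightly less favourable once children with adverse events are retained.

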### Potential risks and adverse events

We conduct active monitoring in both groups for potential risks, especially for the observation group for a natural deterioration in their IXT condition. This risk will be managed biannually for the duration of follow-up period, and the treatment will be offered if needed. Adverse event and serious adverse event following strabismus surgery will be recorded and undertaken properly.

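### A developing constant strabismus is a dropout criterion in the observation arm and no listed outcome counts it, so the natural-course and observation-arm predictor results may be selected toward children who did not progress

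*Protocol article*

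**What the plan says.** Under Objectives, the secondary aims are to "identify the predictive factors affecting long-term outcomes in each group and to observe the natural course of IXT". Under Potential risks and adverse events, both groups are actively monitored, "especially for the observation group for a natural deterioration in their IXT condition".

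Three places describe what happens when an observed child approaches constant strabismus:

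- **Dropout criteria:** the list includes patients in the "control group with a constant strabismus appears to be developing". A parental request for strabismus surgery is joined to this by *or*.
- **Interventions, text below Fig. 2:** "Children in the observation group will be offered surgical treatment if a constant strabismus appears to be developing or parents request surgery", subject to the clinical team's agreement. Leaving the study is not mentioned.
- **Statistical methods:** "The participant will be included in the analysis, once be randomized, regardless of whether or not the assigned intervention is received".

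Proposed outcome measures lists cure (alignment at last follow-up plus a gain in stereoacuity), improvement of the Newcastle control score (NCS), quality of life, and change of refraction. None of these is progression to constant strabismus. Sample size allows for 30% dropout in a total of 280.

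**The concern.** Progression toward constant strabismus is among the most informative events a natural-history objective can observe. The dropout list classes it as a reason for leaving the trial, and because of the *or* it applies even when no operation follows. If leaving means that visits stop, the loss depends on the child's own course. The observation-arm children still measured at 5 years would then be a selected group, and their NCS, deviation angle and stereoacuity would tend to look better than those of all children randomized to observation. A predictor analysis on that group would lack many of the children with the worst courses.

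The likely direction of error is toward concluding that moderate intermittent exotropia is stable without surgery, which the Discussion presents as unsettled. An analysis plan cannot repair this afterwards. Dropout criteria govern which data are collected, and measurements never taken cannot be restored.

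**Working it through.** **1. Does dropout mean loss of data?** The article does not define the term, so the passages have to be set side by side.

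- The sample size is inflated for 30% dropout: 280 × (1 − 0.30) = 196, or 98 per arm. Such an allowance makes sense only if dropouts give no evaluable outcome. The 280 itself cannot be reproduced, because no effect size, SD or cure rates are stated. Working backwards, a standardized difference of 0.40 needs 99 per arm, and 198 / 0.70 = 283, which is close to 280. Nothing below depends on this.
- The text below Fig. 2 attaches only an offer of surgery to the same trigger.
- The intention-to-treat sentence keeps children who did not receive their assigned intervention. It does not supply a final assessment for a child who is no longer seen, and the listed tests use final assessments or scores.

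So either the trigger ends follow-up, and the intention-to-treat statement has no final data for these children, or follow-up continues, and the dropout list is wrong or mislabelled. The text needs changing in both cases.

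**2. Is the event counted elsewhere?** The outcome list does not count it. The data to count it should largely exist: prism and alternate cover test (PACT), NCS and stereopsis are listed under Clinical tests, where "The following clinical assessments are undertaken at each visit".

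**3. Illustrative size.** Inputs from the article: 280 children allocated 1:1, so 280 / 2 = 140 observed. Assumed, because the article gives no such rates: 20% of the 140 have improved NCS (0.20 × 140 = 28), a share q meets the trigger, none of the 28 is among them, and only the remaining children are analysed.

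Improved share among completers = 28 / (140 × (1 − q)).

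| q | Children meeting trigger | Remaining | Improved, completers only | Improved, all 140 kept |
|---|---|---|---|---|
| 10% | 14 | 126 | 28/126 = 22.2% | 20% |
| 20% | 28 | 112 | 28/112 = 25.0% | 20% |
| 30% | 42 | 98 | 28/98 = 28.6% | 20% |

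The last row uses the whole 30% dropout allowance for the arm (0.30 × 140 = 42), so it is a generous upper value if dropout runs as planned.

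The result also depends on who meets the trigger. If those children had improved at the same 20% rate, the completer share would be (28 − 0.20m) / (140 − m) = 20% for any number m removed, and there would be no distortion. The bias arises because children meeting a deterioration trigger are less likely to be those who improved.

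**4. Progression itself.** Under the same completers-only assumption, and if the trigger is not counted, 10-30% of children would be removed for meeting it and progression among those left would read about 0%. With the trigger counted as an event, the denominator stays 140 and the proportion can be estimated.

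**The case against.** The strongest reply is that the article never says these children leave the analysis. The intention-to-treat sentence keeps everyone randomized, the text below Fig. 2 describes only an offer of treatment, and no completers-only analysis is specified. Alignment is judged at last follow-up, so a child who leaves may still contribute a value. Visits before the trigger are recorded, and meeting a listed dropout criterion can itself be counted. Analysis details for the natural-course and predictor objectives may properly sit in a full protocol or analysis plan that is not shown.

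Much of this stands, and it rules out stronger readings that a reader might draw:

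- *The objectives are answered only in children who did not deteriorate.* Not supported. The trigger covers a developing constant strabismus or a parental request. Children whose angle, NCS or stereoacuity worsens short of that remain in follow-up and are measured.
- *The recorded rate of constant strabismus is near zero by construction.* This follows only if completers alone are analysed and the trigger is not counted.
- *Predictors of deterioration cannot be estimated.* Too strong. The event is not provided for as an outcome, and estimates would be biased if these children were treated simply as missing. Surgical-arm predictors are not touched by this trigger.

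What does not stand is the view that the matter can be left to an analysis plan. Whether visits continue after the trigger is a question of data collection, and the article gives conflicting signals on it.

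**Conclusion.** The concern holds as an internal conflict with a foreseeable bias; the article does not establish that these children are excluded. The dropout criteria, the text below Fig. 2 and the statistical methods cannot all be followed as written without a statement of what dropout means. If it ends follow-up, the loss is informative, and the natural-course and observation-arm predictor results are selected toward children who did not progress to constant strabismus.

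The size is unknown. The 22-29% against 20% rests on assumed rates, a completers-only analysis, and no improved child meeting the trigger. If all 140 are kept and assessed, the figure stays at 20%. The point concerns secondary objectives and is inexpensive to correct, so the change should be made, but the primary comparison does not turn on it here.

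**What to change.** 1. Reconcile the dropout criteria, the text below Fig. 2 and the statistical methods so that meeting the trigger does not end study follow-up or data collection. The clinical offer of surgery stays as it is; this change concerns only whether the child continues to be observed.
2. In the observation arm, make the recorded trigger (the clinical team's finding that a constant strabismus is developing) a secondary outcome event, with its date and the NCS, PACT and stereoacuity of that visit. Restrict this to the observation arm, because the trigger is defined only there.
3. Report the cumulative incidence of the event from randomization over the 5 years. Count the trigger as an event and not as censoring, and treat surgery without prior deterioration as a competing event.
4. Use the event as an outcome in the observation-arm predictor analysis.

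**Cost and limits.** This needs a protocol amendment, a few continued visits and one extra analysis. No new procedure is needed, since the measurements are already scheduled and the risk is already managed biannually. Recruitment began in November 2015, so some children had passed 5 years before publication. Visits missed by children dropped earlier cannot be recovered, though their trigger dates may be on record. The trigger is a clinical judgement in a trial where families are told the allocation and the article describes no masked assessment, so it should be reported alongside the serial NCS and PACT measurements.
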